### Statistical Analysis

#### Proposed Data Analyses

For objective 1, we aim to compare respiratory muscle structure and function and PROMs between patients with hEDS or G-HSD and healthy controls and to evaluate the main correlates with dyspnea in patients with hEDS or G-HSD. Descriptive statistics will be used for continuous variables (mean and SD or median and IQR), and frequencies will be used for categorical variables. We will use multivariable regression analysis to compare any differences between groups across respiratory parameters and PROMs, adjusted for EDS subtype (hEDS or G-HSD). We will explore the associations with peak Borg dyspnea scores during CPET using multivariable regression, with possible determinants being MIP, diaphragm thickening fraction, PFC activity, and PFT parameters.

For objective 2, we aim to assess the feasibility of IMT and standard-of-care rehabilitation for improving respiratory muscle strength, exercise capacity, and PROMs compared with standard-of-care rehabilitation alone in patients with hEDS or G-HSD. Descriptive statistics will be used to summarize program adherence, recruitment, participant satisfaction, attrition, and safety in the hEDS or G-HSD study groups. Estimates of within- and between-group differences at T_0_, 4 weeks, and 8 weeks will be reported using means and 95% CI. Paired *t* tests and *t* tests will be used to compare the changes in the primary pilot outcome (MIP) and secondary measures over the 8-week study period within and between the 2 randomized groups.

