### Participants With hEDS or G-HSD

The sample will comprise adult individuals (aged ≥18 years) diagnosed with hEDS or G-HSD by the EDS medical team at Toronto General Hospital based on the 2017 diagnostic criteria [3]. Participants will be included if they have started their participation in the GEAR program within 4 weeks.

The following exclusion criteria will be applied:

Diagnosis of other subtypes of EDS (eg, classical and vascular)Have a cardiac pacemaker, defibrillator, neuromuscular disease, severe autonomic dysfunction, or other cardiovascular manifestations limiting exercise or other exercise contraindicationsRecent respiratory infection (<1 month) or known diagnosis of obstructive or restrictive parenchymal diseaseHistory of pneumothorax, acute otitis media (fluid behind the eardrum), or rupture of tympanic membranes, given the risk owing to IMTParticipation in formal exercise training or IMT program within the last 3 monthsInsufficient English fluency to provide informed consent or inability to follow study protocolsSelf-reported pregnancyNo internet access for IMT or web-based assessments

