### Healthy Controls

Healthy adults (aged ≥18 years) will be age- and sex-matched with the participants with EDS and G-HSD. Individuals will be excluded from the study if they meet the following criteria:

Diagnosis of a respiratory, cardiovascular, or musculoskeletal condition that may contribute to exercise limitationPresence of cardiac pacemaker or implantable defibrillatorInsufficient English fluency to provide informed consent or inability to follow study protocolsSelf-reported pregnancyActive smoker (cigarettes or marijuana)

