#### Sample Size

##### Objective 1

With the prevalence of dyspnea (MRC score: 2 out of 5) in 50% of the patients with hEDS and G-HSD, we estimate that 75% of the patients with hEDS will report a Borg dyspnea score of ≥4 (moderate dyspnea) compared with 25% of healthy controls after cardiopulmonary exercise, as previously observed at our center [74]. Thus, with a sample size of 34 patients with hEDS or G-HSD and 17 healthy controls, we will have 90% power to observe a significant difference in moderate dyspnea (α level=.05). Furthermore, given an estimate of 10 participants for each covariate in multivariable regression modeling, we reckon that enrollment of 34 participants with hEDS or G-HSD will allow us to explore at least 3 determinants of dyspnea in our models.

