## Results

This research was funded in January 2021, and study enrollment began in August 2021 and will continue until December 2023. As of January 2023, a total of 4 participants with hEDS or G-HSD in the intervention group and 4 participants in the usual care group have completed the study, with 5 other participants with hEDS or G-HSD enrolled. A total of 11 healthy controls have completed the study. The results will be submitted for publication once data collection and assessments are complete.

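### The Objective 1 patient-versus-control regression is adjusted for EDS subtype, which controls do not have, so its group coefficient is not the stated patient-minus-control difference

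*Protocol article*

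**What the plan says.** The Proposed Data Analyses section states that Objective 1 is to "compare respiratory muscle structure and function and PROMs between patients with hEDS or G-HSD and healthy controls". The regression named for this is to "compare any differences between groups across respiratory parameters and PROMs, adjusted for EDS subtype (hEDS or G-HSD").

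Subtype is a patient entry diagnosis. Under Participants With hEDS or G-HSD, patients are those "diagnosed with hEDS or G-HSD by the EDS medical team at Toronto General Hospital based on the 2017 diagnostic criteria". Under Healthy Controls, "Healthy adults (aged ≥18 years) will be age- and sex-matched with the participants with EDS and G-HSD". No subtype value or coding is given for controls.

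The Sample Size section for Objective 1 describes an unadjusted comparison of two proportions: "with a sample size of 34 patients with hEDS or G-HSD and 17 healthy controls, we will have 90% power" to detect a difference in moderate dyspnea.

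**The concern.** Adjustment makes sense for a variable that takes values in both groups. Subtype is defined in one group only, and being a patient is the same as having one of the two subtypes. The stated covariate therefore removes no confounding from the patient-control difference. Depending on coding, it leaves the group coefficient undefined or turns it into a comparison of one subtype with controls.

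This regression addresses the first hypothesis of the study: respiratory muscle strength, peripheral airway resistance, quality of life, and anxiety and depression in patients against controls. An analyst who follows the sentence and reads the group coefficient as the patient-control difference would report a quantity that changes with the reference level, which the protocol does not fix.

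**Working it through.** **Inputs.** From the article: 34 patients, 17 controls, subtype with two levels defined in patients only, and for the power statement 75% against 25% with Borg score of 4 or more and α = 0.05 (two-sided assumed). Assumed, because the documents give no figures: the hEDS:G-HSD split (24:10, with 17:17 as a second case) and subtype shifts of 1.0 SD (hEDS) and 0.3 SD (G-HSD) from controls, with residual SD 1.

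**1. The plan's own figure.** Two proportions, 0.75 against 0.25, control:patient ratio k = 0.5, d = 0.50.
- Weighted mean proportion: (0.75 + 0.5 × 0.25)/1.5 = 0.583, and 0.583 × 0.417 = 0.243.
- Uncorrected patients needed for 90% power: [1.96 × √(0.243 × 3) + 1.2816 × √(0.1875 × 3)]² / 0.25 = (1.674 + 0.961)² / 0.25 = 27.8, so 28.
- With continuity correction: (27.8/4) × [1 + √(1 + 2 × 1.5/(27.8 × 0.5 × 0.5))]² = 33.5, so 34 patients and 17 controls.

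This matches the article. Exact enumeration with the continuity-corrected chi-square gives 89.7%. The 90% is reproduced, for a comparison without a subtype term.

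**2. Group term plus both subtype indicators.** Columns are intercept, patient, hEDS and G-HSD. Since patient = hEDS + G-HSD, the 51-row matrix has rank 3 for 4 columns at any split. The group coefficient is aliased. The pooled contrast is still estimable: adding its row (0, 1, 24/34, 10/34) leaves the rank at 3, whereas adding the row for the bare coefficient (0, 1, 0, 0) raises it to 4.

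**3. Group term plus one subtype indicator, controls coded 0.** Rank is 3 of 3. With an hEDS indicator the group coefficient is the G-HSD mean minus the control mean. With a G-HSD indicator it is the hEDS mean minus the control mean. The other subtype's patients contribute only to the residual variance.

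**4. Standard errors, in residual SD.**
- Pooled contrast: √(1/34 + 1/17) = 0.297
- 24:10, G-HSD reference: √(1/10 + 1/17) = 0.399
- 24:10, hEDS reference: √(1/24 + 1/17) = 0.317
- 17:17, either reference: √(1/17 + 1/17) = 0.343

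**5. Estimate and power at 24:10 under the assumed shifts** (simulation, two-sided 5%).

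| Model | True coefficient (SD) | Mean SE | Power |
|---|---|---|---|
| Group only | (24 × 1.0 + 10 × 0.3)/34 = 0.79 | 0.31 | about 72% |
| Subtype term, G-HSD reference | 0.30 | 0.40 | about 11% |
| Subtype term, hEDS reference | 1.00 | 0.32 | about 87% |

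The group-only SE is slightly above 0.297 because the subtype difference is left in the residual.

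**6. Equal subtype effects (0.8 SD each), 24:10.** The coefficient is 0.8 under either reference, so the estimate does not shift. Power is about 50% (G-HSD reference) or 70% (hEDS reference), against 75% pooled.

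**The case against.** The strongest reply is that the four-column model, the one-indicator model and a three-level factor span the same column space and give the same fitted values. The patient-minus-control difference can be recovered from any of them, and coding and contrasts are commonly left by a condensed article to the analysis plan. This stands in part: a reader might infer that the patient-control difference cannot be estimated at all, and that would be too strong. But the article does more than omit coding. It names an adjustment that has no meaning for this contrast, and an analysis plan that repeats the sentence inherits the problem unless it adds a contrast. Nor can the adjustment be reassigned to another analysis: the model for determinants of dyspnea is in a separate sentence, and the randomised comparison falls under Objective 2, with t tests.

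Four stronger readings are not supported:
- **That the model always loses power.** The 11% is one reference level under assumed effects. The other gives 87%, above the pooled contrast, and with equal subtype effects only precision suffers.
- **That controls were enrolled ahead of the patients they match.** The Results section reports "A total of 11 healthy controls have completed the study" when 4 + 4 + 5 = 13 patients had completed or were enrolled. Reading this as controls running ahead needs 2:1 matched sets, which the article does not describe. The 34 and 17 are final totals, and 11 controls could each match a different one of the 13 patients.
- **That age and sex are ignored.** They are handled by matching, and naming one covariate does not show that all others are excluded. Including them is a sensible addition, not the defect.
- **That the stated 90% power is wrong.** It reproduces for the comparison it describes.

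**Conclusion.** The point holds, at moderate severity. The stated model does not deliver the stated contrast through its group coefficient: that coefficient is either aliased or a comparison of one subtype with controls. This follows from the definitions and does not depend on any assumed number.

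Its size does depend on assumptions. The SE rises from 0.30 to 0.32 or 0.40 residual SD at an assumed 24:10 split, and to 0.34 at 17:17. Under the assumed shifts of 1.0 and 0.3 SD, power is about 11% or 87% depending on the reference level, against about 72% for the pooled comparison. Equal subtype effects would remove the shift in the estimate but not the loss of precision.

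The primary pilot outcome, MIP change in the randomised groups, is untouched. So are the Objective 1 sample size statement, allocation and data collection.

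**What to change.** Replace the sentence with one of two forms.
- **Preferred:** compare patients with controls by regression with a group term and no subtype term, with the matching factors age and sex as covariates.
- **Alternative:** fit one three-level factor (control, hEDS, G-HSD) and state in advance the pooled patient-versus-control contrast and its weights (for example, in proportion to the subtype numbers).

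In either case, examine hEDS against G-HSD among patients only.

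The cost is one sentence, made before analysis. Age and sex are already collected and, entered linearly, use two degrees of freedom. No new data, extra participants or change to study conduct is needed.

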**Methods:**

The study will include 34 participants with hEDS or G-HSD and 17 healthy, age- and sex-matched controls to compare respiratory muscle structure and function and PROMs. After baseline assessments, participants with hEDS or G-HSD will be randomized into the intervention group and provided IMT combined with Ehlers-Danlos Syndrome standard-of-care rehabilitation or into the usual care group, and provided only standard-of-care rehabilitation for 8 weeks. The intervention group will be prescribed IMT in their home environment using the POWERbreathe K5 IMT device (POWERbreathe International Ltd). IMT will comprise 2 daily sessions of 30 breaths for 5 days per week, with IMT progressing from 20% to 60% of the baseline maximal inspiratory pressure (MIP) over an 8-week period. Feasibility will be assessed through rates of recruitment, attrition, adherence, adverse events, and participant satisfaction. The primary pilot outcome is MIP change over an 8-week period in hEDS or G-HSD. Secondary outcomes will include the evaluation of dyspnea using Medical Research Council Scale and 18-point qualitative dyspnea descriptors; diaphragmatic thickening fraction using ultrasound; respiratory muscle endurance; pulmonary function; prefrontal cortical activity using functional near-infrared spectroscopy; aerobic capacity during cardiopulmonary exercise testing; quality of life using Short Form-36; and scores from the Depression, Anxiety, and Stress scale-21. These measures will also be performed once in healthy controls to compare normative values. Multivariable regression will be used to assess the contributors to dyspnea. Paired 2-tailed *t* tests will be used to assess the changes in MIP and secondary measures after 8 weeks of IMT.

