### Randomization

After T_0_ assessments, the participants will be randomly allocated to the intervention or usual care group using a 1:1 ratio stratified by hEDS or G-HSD. The allocation of the participants to their groups will be randomized (blocks of 2 to 4) using shuffled, opaque envelopes by a biostatistician. The study participants and the research team and coordinator supervising the IMT will be aware of the group assignments.

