
#### Primary Pilot Outcome

The primary pilot outcome will be the change in MIP over the 8-week study period to demonstrate the efficacy of IMT, which has been shown to be an important physiological measure in several IMT studies [11,26,35,73].

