##### Objective 2 (Primary Pilot Outcome)

Given an estimated MIP comparable with that of moderate COPD patients (mean 51, SD 15 cm H_2_O), we anticipate a mean increase of 10 (SD 3.5) cm H_2_O in MIP in the IMT and exercise training group compared with the hEDS or G-HSD usual care group (exercise training alone; 5 cm H_2_O) [75]. Assuming a maximum attrition rate of 20% among the 34 RCT participants with hEDS or G-HSD, we will have 90% power (α=.05) to observe a significant difference in MIP with 17 participants per group.

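### The between-arm t tests on 8-week change leave out baseline as a covariate and the hEDS/G-HSD stratum; adjusting for both is a modest, nearly free gain in precision, not the repair of an error

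*Protocol article*

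**What the plan says.** All references are to the protocol article.

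- **Primary Pilot Outcome:** "The primary pilot outcome will be the change in MIP over the 8-week study period".
- **Proposed Data Analyses, objective 2:** the methods are paired t tests inside each arm and two-sample t tests across arms, worded as follows: "tests will be used to compare the changes in the primary pilot outcome (MIP) and secondary measures over the 8-week study period". Means with 95% CIs are to be reported. Neither a baseline covariate nor a subtype term is named.
- **Randomization:** patients are allocated "using a 1:1 ratio stratified by hEDS or G-HSD".
- **Proposed Data Analyses, objective 1:** the comparison of patients with healthy controls is a regression adjusted for subtype. The randomised comparison, in which subtype is the stratification factor, has no such term.
- **Sample Size, Objective 2:** the baseline level is borrowed from another disease: "Given an estimated MIP comparable with that of moderate COPD patients (mean 51, SD 15 cm H_2_O"). The assumed effect in the trained arm is stated next: "we anticipate a mean increase of 10 (SD 3.5) cm H_2_O in MIP in the IMT and exercise training group". It is set against the "usual care group (exercise training alone; 5 cm H_2_O"). After allowing for up to 20% attrition, the claim is "we will have 90% power (α=.05) to observe a significant difference in MIP with 17 participants per group".

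**The concern.** When randomisation is stratified and the outcome is also measured at baseline, a model containing the stratum and the baseline value normally gives the most precise arm difference. A two-sample t test on change uses neither as a covariate, and two small losses can follow.

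1. **Baseline.** The change score fixes the coefficient of baseline at 1. With equal SDs at the two visits, the true regression slope equals the pre-post correlation r, which is below 1. The change score then over-corrects, and a fraction (1 − r) of any chance baseline difference passes into the estimate with opposite sign.
2. **Stratum.** If subtype predicts the change in MIP, stratification has balanced that variation between arms, yet the t test still counts it as error. The interval is then wider than it need be.

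The same test is stated for all secondary measures. With 17 per arm and possibly 13 to 14 completers, sizeable chance imbalances are likely, so it is worth checking how far they reach the result.

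**Working it through.** **Inputs.** From Sample Size, Objective 2: baseline SD 15, SD of change 3.5 (given for the IMT arm; assumed here for both arms), changes of 10 and 5 (difference 5 cm H2O), alpha 0.05, 17 per arm, attrition up to 20%, so 17 × 0.8 = 13.6, or about 14 evaluable per arm. The test is taken as two-sided; the abstract says 2-tailed for the paired tests. The documents give no pre-post correlation.

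**1. The plan's power figure.** With difference 5 and SD 3.5, the two-sample t test has 93.7% power at 13 per arm, 95.3% at 14 and 98.1% at 17. The stated 90% is not matched exactly, but it errs on the cautious side.

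**2. Size of a chance baseline imbalance.** SE of the baseline MIP difference = 15 × √(2/n).
- n = 17: 5.14 cm H2O; P(|difference| ≥ 5) = 2 × (1 − Φ(5/5.14)) = 33%.
- n = 14: 5.67 cm H2O; the probability is 38%.

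These figures describe baseline means, not the estimated treatment effect.

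**3. Correlation implied by the plan.** With equal SDs at both visits, SD(change)² = 2 × 15² × (1 − r), so r = 1 − 3.5²/(2 × 15²) = 1 − 12.25/450 = 0.973.

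**4. What reaches the estimate, and what adjustment gains.**
- Shift in the change-score estimate for an imbalance of 5 = (1 − r) × 5.
- Large-sample variance ratio, adjusted to change score = (1 − r²)/(2(1 − r)) = (1 + r)/2.
- Estimating the slope costs a factor of 1 + 1/(N − 5) in a model with arm, baseline and stratum. With N = 28 this is 1 + 1/23 = 1.043.

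| r | SD of change implied | Shift per 5 cm H2O | (1 + r)/2 | Ratio at 14 per arm |
|---|---|---|---|---|
| 0.973 (plan's SDs) | 3.5 | 0.14 | 0.986 | 1.03 |
| 0.9 (assumed) | 6.7 | 0.5 | 0.95 | 0.99 |
| 0.7 (assumed) | 11.6 | 1.5 | 0.85 | 0.89 |
| 0.5 (assumed) | 15.0 | 2.5 | 0.75 | 0.78 |

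A simulation of 40,000 trials per row (14 per arm, stratum not prognostic) agrees: at r = 0.973 the adjusted variance is about 3% higher, at r = 0.9 about 1% lower, at r = 0.7 about 11 to 12% lower, and at r = 0.5 about 21 to 22% lower. At r = 0.973, power is 95.3% unadjusted and about 94.6% adjusted.

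**5. Sensitivity to equal SDs.** Holding the SD of change at 3.5 and letting the 8-week SD run from 14 to 18 (assumed), a one-SE imbalance of 5.14 shifts the estimate by between −0.5 and +1.0 cm H2O.

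**6. Stratum.** The documents give neither the subtype split nor any subtype difference in MIP change, so the gain cannot be sized. As illustration only: with a 50:50 split and subtype mean changes differing by g, the share of the change variance removed is 0.25 × g²/3.5². That is 2%, 8% or 25% for g = 1, 2 or 3.5 cm H2O.

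**The case against.** The strongest defence is that nothing here is wrong. A two-sample comparison of change between randomised arms is unbiased over randomisation, and omitting a stratification factor leaves the test valid or conservative. The study is a feasibility pilot that reports estimates with intervals. Adjusted analyses may also sit in an analysis plan that is not shown. On the plan's own SDs the adjusted model is marginally less precise for MIP. All of this stands, and it limits the point to an improvement.

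A reader might infer two stronger things, which the documents do not support.

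- *That the test disregards baseline MIP, so the result is exposed to an imbalance as large as the 5 cm H2O target.* The change score subtracts baseline. The one-in-three chance of a 5 cm H2O difference concerns the baseline means; only the (1 − r) share reaches the estimate, 0.14 cm H2O on the plan's figures.
- *That adjustment saves 15% or 25% of the variance.* Those are large-sample values at r = 0.7 and 0.5, before the cost of estimating the slope. Those correlations also require an SD of change of 11.6 or 15, three to four times the planned 3.5. In that case the larger problem would be the planning SD: at r = 0.7 and 14 per arm, power is about 20% unadjusted and 21 to 22% adjusted, so adjustment would not rescue the trial.

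The defence does not cover everything. The article states the method for the randomised comparison, and it adjusts for subtype under objective 1 but not where subtype was the stratifier. It also gives no basis for a correlation near 0.97 in the secondary outcomes, to which the same test applies.

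**Conclusion.** The point holds as a modest precision improvement. The stated between-arm analysis is valid, but it does not match the stratified design and uses baseline only by subtraction.

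For MIP, under SDs of 15 and 3.5 with equal SDs at both visits, the consequence is negligible: a shift of 0.14 cm H2O per 5 cm H2O of imbalance, and precision essentially unchanged. It becomes material only if the SD of change is well above 3.5. At an assumed r of 0.7 the shift is 1.5 cm H2O, or 30% of the target difference, and adjustment lowers the variance by about 11%. At an assumed r of 0.5 the shift is 2.5 cm H2O and the variance falls by about 21 to 22%. The benefit of including the stratum is of unknown size.

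The case for change rests on three things: agreement between design and analysis, the secondary outcomes for which no high correlation is documented, and protection if MIP proves more variable than planned.

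**What to change.** State in Proposed Data Analyses, objective 2, that the between-arm comparison of MIP and of each continuous secondary outcome will use a linear model of the 8-week value on arm, baseline value and stratum (hEDS or G-HSD), reporting the adjusted arm difference with its 95% CI. The primary pilot outcome need not be redefined: once baseline is in the model, the arm coefficient is the same whether the response is 8-week MIP or change in MIP. The unadjusted t test can be kept as a supporting analysis.

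The cost is a change of wording and two degrees of freedom, with no new data. If the correlation is as high as the sample-size SDs imply, the variance for MIP rises by up to about 3% and power at 14 per arm stays at about 95%.

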#### Secondary Outcomes

The secondary outcome measures evaluated will include dyspnea, respiratory muscle structure and function, mood, and HRQL assessed at T_0_ and 8 weeks, as shown in Table 3.

**Table 3 table3:** Study outcomes.

Outcome				Assessment measurement		Time point

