## Discussion

### Summary

This study will help characterize the multifactorial nature of dyspnea experienced by individuals with hEDS and G-HSD. Given the known impairments in respiratory muscle strength in this population, this study will allow us to assess the synergistic effects of IMT and standard-of-care rehabilitation on dyspnea, PROMs, and exercise capacity, which have not been previously characterized. The findings of this study will inform the feasibility of a larger study using IMT and standard-of-care rehabilitation that will be appropriately powered to assess the effects of IMT on PROMs and clinical outcomes. Furthermore, this study has the potential to inform our understanding of the mechanistic effects that IMT may have on diaphragm structure and function, lung physiology, and neurocognitive adaptations in this population.

The literature describing respiratory manifestations in EDS and G-HSD has generally been limited to a few observational studies and case series involving mainly 4 subtypes: classical EDS, vascular EDS, hEDS, and G-HSD [2,9]. We chose to focus on the population with hEDS, as hEDS comprises the major subtype of EDS, and there is also a study highlighting respiratory muscle weakness and effectiveness of IMT [11]. The population with G-HSD was also chosen, as G-HSD is defined to be on the continuum of EDS and represents one of the most common diagnoses in our GEAR rehabilitation program, and the respiratory sequelae of G-HSD have not been well characterized [3]. Another important consideration factored into our selection of the EDS population was the risk of pneumothorax, which is generally lower in individuals with hEDS and G-HSD than in those with other subtypes. Thus, the inclusion of patients with hEDS and patients with G-HSD is owing to the representation of the majority (>90%) of the patients with EDS followed in our program.

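### Within-arm paired tests on MIP and about 27 secondary measures cannot show an effect of IMT, because both arms train; rest any such statement on the between-arm difference and treat secondary comparisons as exploratory

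*Protocol article*

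**What the plan says.** The article's Proposed Data Analyses section, under objective 2, says of its paired and unpaired t tests that they "will be used to compare the changes in the primary pilot outcome (MIP) and secondary measures over the 8-week study period within and between" arms. It also promises within- and between-group estimates as means with 95% CIs.

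The abstract's Methods paragraph is narrower. It gives only "Paired 2-tailed" t tests and says these "tests will be used to assess the changes in MIP and secondary measures after 8 weeks of IMT". It mentions no comparison between arms.

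Under Secondary Outcomes, "The secondary outcome measures evaluated will include dyspnea, respiratory muscle structure and function, mood, and HRQL", and Table 3 lists the individual measures. MIP is the one named primary pilot outcome. The sample-size section for objective 2 says "we anticipate a mean increase of 10 (SD 3.5) cm H_2_O in MIP in the IMT and exercise training group", against 5 cm H2O in usual care, and "we will have 90% power (α=.05) to observe a significant difference in MIP with 17 participants per group". No significance level is given for the secondary measures.

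The Discussion summary says "this study will allow us to assess the synergistic effects of IMT and standard-of-care rehabilitation on dyspnea, PROMs, and exercise capacity". It then says the findings will inform a larger study "that will be appropriately powered to assess the effects of IMT on PROMs and clinical outcomes".

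**The concern.** Usual care here is an active comparator. Study Arms and Table 2 give both groups the same aerobic, resistance, stabilization and balance training, and only the IMT differs. The Discussion expects aerobic and strength training by itself to strengthen the respiratory muscles and improve exercise capacity. Change from baseline in the IMT arm therefore mixes the effect of IMT with that of rehabilitation, repeat testing and regression to the mean. A paired test in that arm asks whether anything changed, not whether IMT changed it.

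The abstract nevertheless presents the paired tests as the assessment after IMT, and the analysis section repeats them for every secondary measure in both arms. The risk is that measures are reported as responding to IMT because they reached significance in one arm and not in the other. Such a result could then guide the choice of outcome for the larger trial.

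A lesser issue is the number of between-arm comparisons in a 34-patient pilot, with no statement that those on secondary measures are exploratory.

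**Working it through.** **Number of secondary measures (Table 3, with the SF-36 and mood-scale descriptions).** Spirometry and volumes 4, oscillometry 3, endurance 1, diaphragm 2, dyspnea 3, Godin 1, SF-36 2 (component scores), Depression, Anxiety, and Stress scale 3, exercise capacity 4, heart rate 2, prefrontal activity 2. The sum is 27. Counting the SF-36 and the mood scale once each gives 27 - 5 + 2 = 24. Counting eight SF-36 domains instead of two component scores gives 27 - 2 + 8 = 33.

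**The plan's own figure.** Inputs from the sample-size section: difference 10 - 5 = 5 cm H2O, SD 3.5 (stated for the IMT arm, assumed in both), two-sided alpha .05. Between-arm power is 98.1% (t) to 98.6% (normal) with 17 per arm, 95.3% to 96.6% with 14, and 93.7% to 95.4% with 13. The stated 90% after 20% attrition is conservative. The powered comparison is the between-arm one, and this point does not disturb it.

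**Within-arm test of MIP in usual care, on the plan's figures.** Noncentrality = sqrt(n) x mean change / SD.
- n = 17: sqrt(17) x 5 / 3.5 = 5.89; critical t on 16 df = 2.12; probability of significance above 0.99.
- n = 13 completers: sqrt(13) x 5 / 3.5 = 5.15; critical t on 12 df = 2.18; probability 0.997.

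On the protocol's assumptions, the arm without IMT would almost surely show a significant rise. The same result in the IMT arm therefore says nothing specific about IMT.

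**Secondary measures: significant with IMT but not with usual care, when IMT adds nothing.** Suppose both arms truly change by d SDs (assumed), with 17 per arm. Let p be the power of the paired test at .05. The arms are independent, so the probability of this pattern is p(1 - p).

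| d | p | p(1 - p) |
|---|---|---|
| 0.3 | 0.214 | 0.168 |
| 0.5 | 0.491 | 0.250 |
| 0.7 | 0.773 | 0.175 |

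With 13 completers and d = 0.5, p = 0.382 and the product is 0.382 x 0.618 = 0.236. The mirror pattern, favouring usual care, is equally frequent.

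**Between-arm tests on 27 measures, .05 each (assumed), no true differences.** Expected false positives: 27 x 0.05 = 1.35. If independent, the chance of at least one is 1 - 0.95^27 = 0.75 in either direction, and 1 - 0.975^27 = 0.50 favouring IMT. With a common correlation between measures:

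| Correlation | Either direction | Favouring IMT |
|---|---|---|
| 0 | 0.75 | 0.50 |
| 0.3 | 0.63 | 0.33 |
| 0.5 | 0.48 | 0.24 |
| 0.8 | 0.25 | 0.12 |

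Under independence, 24 measures give 0.71 and 33 give 0.82 in either direction.

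**The case against.** The strongest reply is that this is a feasibility pilot with one named primary outcome. Everything else is called secondary, between-arm tests and 95% CIs are already planned, and powered assessment of patient-reported and clinical outcomes is left to a larger study. A condensed article may also leave multiplicity rules to an analysis plan that is not shown. Most of this stands. The absence of a multiplicity rule is not a fault in itself, and the pilot framing supplies part of an exploratory label. It does not answer the point about the paired tests, which the article states rather than omits.

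Several stronger readings are tempting but not supported:
- A reader might infer that secondary measures are tested at the full .05. The document attaches that level only to its two sample-size calculations, so .05 per test is an assumption here.
- A reader might pool all 27 x 3 = 81 within- and between-arm tests into one error rate. That requires no change in either arm, which the plan itself does not expect. It also ignores that the two arms are independent and that each between-arm test is built from both.
- A reader might say that a false benefit of IMT is likely. Counting only results that favour IMT, the chance is at most about one half, and about a quarter at correlation 0.5.
- A reader might take the abstract's Conclusions as a promise to demonstrate effectiveness. They promise a better understanding of it and say that IMT may help.

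**Conclusion.** The point holds as a cheap improvement to a stated analysis. The within-arm tests cannot support a statement about IMT, because both arms receive active training and the protocol expects a gain in MIP without IMT. For MIP, a significant paired test in usual care is nearly certain (above 0.99, assuming SD 3.5 in that arm). For secondary measures, contrasting significance between arms would mislead in about 25% of measures if both arms change by 0.5 SD, and in 17% to 18% at 0.3 or 0.7 SD. These effect sizes are assumptions, since the article gives none for secondary measures.

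The between-arm multiplicity is a supporting consideration that depends on an assumed .05 per test, no true differences and a common correlation. It justifies an exploratory label. It does not show that formal alpha control or a testing hierarchy is required in a pilot of this size. The planned between-arm comparison of MIP is unaffected.

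**What to change.** In the abstract's Methods and in Proposed Data Analyses:
1. State that any conclusion about the effect of IMT, on MIP or a secondary measure, rests on the between-arm difference in change with its 95% CI.
2. Report within-arm changes descriptively (mean change with 95% CI) and remove the paired tests.
3. Call the between-arm comparisons of secondary measures exploratory, in line with the Discussion's deferral of powered assessment, and word its sentence on synergistic effects to match.

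This takes a few sentences. It needs no new data, assessments or participants, and the estimates are already planned. The cost is that within-arm and secondary p values can no longer be offered as evidence of effectiveness.
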